# Effects of Increased Standing and Light-Intensity Physical Activity to Improve Postprandial Glucose in Sedentary Office Workers: Protocol for a Randomized Crossover Trial

**DOI:** 10.2196/45133

**Published:** 2023-08-23

**Keywords:** sitting bouts, digital health intervention, standing desk, endothelial function, glycemic control, sleep, blood pressure, insulin, mHealth

## Abstract

**Background:**

Prolonged bouts of sedentary time, independent from the time spent in engaging in physical activity, significantly increases cardiometabolic risk. Nonetheless, the modern workforce spends large, uninterrupted portions of the day seated at a desk. Previous research suggests—via improved cardiometabolic biomarkers—that this risk might be attenuated by simply disrupting sedentary time with brief breaks of standing or moving. However, this evidence is derived from acute, highly controlled laboratory experiments and thus has low external validity.

**Objective:**

This study aims to investigate if similar or prolonged cardiometabolic changes are observed after a prolonged (2-week) practice of increased brief standing and moving behaviors in real-world office settings.

**Methods:**

This randomized crossover trial, called the WorkWell Study, will compare the efficacy of two 2-week pilot intervention conditions designed to interrupt sitting time in sedentary office workers (N=15) to a control condition. The intervention conditions use a novel smartphone app to deliver real-time prompts to increase standing (STAND) or moving (MOVE) by an additional 6 minutes each hour during work. Our primary aim is to assess intervention-associated improvements to daily postprandial glucose using continuous glucose monitors. Our secondary aim is to determine whether the interventions successfully evoke substantive positional changes and light-intensity physical activity (LPA). Other outcomes include the feasibility and acceptability of the intervention conditions, fasting blood glucose concentration, femoral artery flow-mediated dilation (f-FMD), and systolic and diastolic blood pressure.

**Results:**

The trial is ongoing at the time of submission.

**Conclusions:**

This study is a novel, randomized crossover trial designed to extend a laboratory-based controlled study design into the free-living environment. By using digital health technologies to monitor and prompt participants in real time, we will be able to rigorously test the effects of breaking up sedentary behavior over a longer period of time than is seen in traditional laboratory-based studies. Our innovative approach will leverage the strengths of highly controlled laboratory and free-living experiments to achieve maximal internal and external validity. The research team’s multidisciplinary expertise allows for a broad range of biological measures to be sampled, providing robust results that will extend knowledge of both the acute and chronic real-life effects of increased standing and LPA in sedentary office workers. The WorkWell Study uses a rigorous transdisciplinary protocol that will contribute to a more comprehensive picture of the beneficial effects of breaking up sitting behavior.

**Trial Registration:**

ClinicalTrials.gov NCT04269070; https://clinicaltrials.gov/study/NCT04269070

**International Registered Report Identifier (IRRID):**

DERR1-10.2196/45133

## Introduction

Society is rapidly evolving to embrace the technological advances in communication, entertainment, and transportation that have benefited nearly every sector of daily life. These advances have also contributed to the accumulation of time spent engaging in sedentary behaviors, with approximately 60% of waking hours spent sedentary [1]. Sedentary behavior (defined by the Sedentary Behavior Research Network as <1.5 metabolic equivalents in a seated posture) [2] is a growing public health concern due to its well-established links to cardiometabolic disease development and premature mortality, independently from time spent in moderate to vigorous physical activity (MVPA) [3-7]. Meeting the recommended 150 minutes per week of MVPA is associated with beneficial cardiometabolic health outcomes [8-11]. However, MVPA alone does not offset the numerous negative health outcomes associated with prolonged bouts of inactivity. Research suggests that for each additional hour spent sedentary, the likelihood of developing metabolic syndrome and type 2 diabetes increases by 39% and 22%, respectively [12]. Therefore, reducing time spent in prolonged bouts of inactivity may lead to favorable long-term health outcomes [13].

Breaking up prolonged bouts of sitting attenuates the negative health outcomes associated with sedentary behavior [14-20], likely due to postural change and contraction of large skeletal muscle groups [13]. These actions result in increased vascular blood flow and shear stress via gravitational pull and the skeletal muscle pump, thus increasing venous return, decreasing blood pooling in the lower limbs, and activating contraction- and insulin-mediated glucose uptake pathways [21]. Taking a break to stand, walk, or exercise—in some cases, for as little as 2 minutes for every 20 minutes spent sitting [14,17]—improves glycemic control [14-19,22], insulin sensitivity [16,17], vascular response [14,23], and cardiometabolic health outcomes [16,19].

Adults spend 7.7 to 11.5 hours per day engaging in sedentary time [4,24,25], with modern office-based employees spending more than 89% of their workday seated [20]. This sedentary time, however, might be reduced through various intervention techniques. A meta-analysis reported that environmental (eg, sit-stand workstation at work) and multicomponent (eg, sit-stand workstation, education, and mobile app) intervention approaches resulted in sedentary time reductions of 40.6 and 35.5 minutes per day, whereas behavioral interventions (eg, education) resulted in a modest reduction of 23.87 minutes of sedentary time [26]. Studies using isotemporal modeling indicate that replacing sitting bouts of 30-60 minutes with either light-intensity physical activity (LPA) or MVPA is associated with reduced risk for all-cause and cardiovascular mortality, and improved cardiometabolic risk biomarkers, particularly in adults who are less active [27,28]. These findings support the feasibility and efficacy of interventions targeting sedentary time reduction and resulting health benefits [26-31].

Intervention-based research aimed at reducing sitting time and improving health outcomes has typically been conducted in tightly controlled laboratory environments, and the few studies conducted in real-world settings lack the intensive clinical and behavioral measures of a laboratory-based study. Thus, workplace-based efficacy and feasibility studies incorporating rigorous procedures with high internal validity are needed to better evaluate interventions aimed at reducing sitting time. The protocol described is a workplace study using evidence-based intervention components along with mobile and wearable technologies. A randomized crossover design will be used to explore cardiometabolic outcomes resulting from the addition of brief periods of standing or LPA during work hours while also assessing the efficacy and feasibility of the intervention in the real-world office setting.

## Methods

### Study Aims

The primary aim of this study is to examine the impact of 2 different intervention conditions (STAND and MOVE) on 3-hour postlunch postprandial glucose compared to the baseline control condition. Interventions entail adding 6 minutes per hour to baseline standing and LPA minutes during the workday. We hypothesize that both intervention conditions will improve postprandial glucose regulation. The secondary aim is to assess intervention adherence and changes in standing and LPA. Exploratory aims include (1) assessing participant acceptability and satisfaction during the intervention; and assessing intervention-induced changes in (2) sleep, (3) anthropometrics and body composition, (4) endothelial function, (5) central and peripheral blood pressure, (6) fasting blood glucose concentration, (7) fasting insulin concentration, (8) fasting high-density lipoprotein (HDL) concentration, (9) low-density lipoprotein (LDL) oxidation, (10) fasting triglycerides, (11) total antioxidant capacity (TAC), (12) hemoglobin A_1c_ (HbA_1c_), (13) microbial diversity of the gut, (14) metabolomics from stool and plasma, and (15) DNA variants that may explain differences in response to the intervention.

### Study Design

The WorkWell Study is a pilot 6-week randomized crossover design with 2 balanced arms. Across 2 intervention periods, all participants (N=15) will experience both workplace interventions following a baseline control condition: (1) MOVE, an intervention targeting 6-minute increase in baseline LPA each work hour and (2) STAND, an intervention targeting 6-minute increase in baseline standing each work hour via a sit-stand workstation. Participants will wear a Bluetooth accelerometer and will be prompted with a mobile app during each intervention period. The intervention sequence is randomized and a washout period of at least 1 week will occur between interventions to reduce any potential carryover effect. Clinic-based assessments will occur at baseline and after each intervention period is completed (Figure 1).

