#### Baseline Period

Once enrolled and initial baseline measures taken, participants will go through a 1-week baseline period in which they are outfitted with multiple devices that they will wear during each intervention period: a continuous glucose monitor (FreeStyle Libre, Abbott Diabetes Care), activPAL micro (PAL Technologies), and GENEActiv accelerometer (ActivInsights). These devices will be worn continuously (ie, 24 hours per day) for 7 consecutive days to assess baseline glycemic response, activities (including sitting, standing, and lying behaviors), and sleep, respectively. Participants will engage in their normal behaviors during the week-long baseline period.

Lunch will be delivered on workdays during the baseline period and both intervention periods. Participants will select options from a standardized menu (approximately 33% of daily caloric needs is equal to 660 kcals, with macronutrient composition of 55% carbohydrate is equal to approximately 90.75 g, 30% fat carbohydrate is equal to approximately 22 g, 15% protein [±10%] is equal to 24.75 g) created from a list of local vendors. The standardized meal choices will be consistently repeated each week during the trial, with the same meals provided Monday to Friday during baseline and both intervention periods. Participants will be asked to avoid eating or drinking (with the exception of water and black coffee or tea) 3 hours before and post lunchtime. Food logs will be used to report when they started and finished eating their lunch, how much food they ate, and the exact food consumed during the trial.

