#### Randomization

After completion of the baseline period, each participant will be randomized to an intervention sequence (MOVE-STAND or STAND-MOVE). Randomization is completed using the REDCap (Research Electronic Data Capture; Vanderbilt University) randomization tool and a preloaded table with treatment sequences [32,33].

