#### Interventions

The MOVE and STAND interventions will be delivered across 2 work weeks (approximately 10 days). Both use the WorkWell mobile app and Bluetooth Activator micro (PAL Technologies) device as intervention tools in conjunction with the equipment worn during the baseline period (Figure 2). The primary behavioral target of the MOVE intervention will be to increase baseline LPA time by an additional 6 minutes per hour during work. Similarly, the primary behavioral target of the STAND intervention will be to increase baseline standing time by an additional 6 minutes per hour during work. This target of adding 6 minutes per working hour of standing and LPA was selected as an achievable goal with evidence for cardiometabolic health improvements [14-19,22].

After the baseline period is completed, the self-reported work hours and corresponding activPAL micro data will be used to identify the average minutes of standing and moving for each hour of the participant’s workday. The intervention goals will be identified for each participant by adding 6 minutes to these hourly averages. For example, if a participant stands for an average of 10 minutes per work hour during the baseline period, their STAND intervention goal will be 16 minutes of standing per work hour. The same approach will be used to identify MOVE intervention goals. The WorkWell app will use live feedback from the Bluetooth Activator micro to prompt participants in the STAND intervention to meet their hourly standing goals using a sit-stand workstation, while the MOVE intervention will prompt participants to engage in light-intensity movements (eg, walking) to meet their hourly goals.

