## Discussion

### Comparison to Prior Work

While low levels of physical activity have been a public health concern, there is evidence that sedentary behavior duration may also confer health risks [13]. Observational studies suggest that breaking up sedentary time is associated with improved cardiometabolic health [58]. These free-living, mainly observational studies have demonstrated the theoretical feasibility of workplace interventions, yet cannot control for potentially confounding factors, obscuring the meaningful analysis of the relationship. Laboratory studies, however, suggest a causal relationship between decreased sedentary time and cardiometabolic health [59]. While these studies are tightly controlled in both the environment and intervention, they lack important context regarding the translation of these findings into real-world settings.

The WorkWell Study is a novel randomized controlled crossover trial that has been designed to extend laboratory-based, controlled study designs into the natural environment of the workplace. To accomplish this, we have used digital health technologies to monitor and prompt participants in real time while maintaining rigorous adherence to increased standing and moving regimes. This innovation will allow us to test the effects of breaking up sitting with standing and LPA over a longer period of intervention than has been used in traditional laboratory-based studies. Additionally, we have included a broad set of concomitant biological measures, including dynamic changes in postprandial and 24-hour glucose, as well as outcomes in the emerging areas of metabolome and gut microbiome composition. We will use two 2-week interventions targeting behavior change to decrease sitting time in the workplace as well as to improve cardiometabolic health and to assess behavior change. This study was carefully designed to extend laboratory-based studies—both in duration, as well as translation into more ecological settings—thus providing more evidence on the causal role of interrupted sitting time (with standing and moving) on cardiometabolic health. As a result, we will be able to address (1) statistical association via baseline and washout weeks that allow participants to serve as their own controls, (2) temporality via continuous accelerometer tracking and prescheduled laboratory visits, and (3) nonspuriousness via randomized assignment and controlled treatment dosage.

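### STAND and MOVE versus control is a nonrandomized before-after comparison, but the Discussion credits randomized assignment without limiting it to MOVE versus STAND

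*Protocol article*

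**What the plan says.** All references are to the Protocol article.

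- **Primary contrast.** Study Aims sets out to examine the effect of STAND and MOVE "on 3-hour postlunch postprandial glucose compared to the baseline control condition".
- **Position of control.** Under Study Design, "all participants (N=15) will experience both workplace interventions following a baseline control condition". Under Baseline Period, "participants will go through a 1-week baseline period".
- **What is randomized.** Under Randomization: "After completion of the baseline period, each participant will be randomized to an intervention sequence (MOVE-STAND or STAND-MOVE"). No sequence places control second or third, and there is no parallel control group.
- **Lengths.** Under Interventions: "The MOVE and STAND interventions will be delivered across 2 work weeks (approximately 10 days"). Study Design adds a washout of at least 1 week and gives carryover as its purpose.
- **When glucose is measured.** Table 1 has three columns: Baseline, Intervention 1 and Intervention 2. Primary Outcomes places the glucose sensor for those same periods.
- **Model.** Statistical Analysis Plan: a linear mixed model with intervention, sequence and time period (1 or 2) as fixed factors, for three repeated measurements per person.
- **Claims.** Comparison to Prior Work says the design adds evidence on the causal role of interrupting sitting. It lists, first, "statistical association via baseline and washout weeks that allow participants to serve as their own controls" and, third, "nonspuriousness via randomized assignment and controlled treatment dosage". Strengths and Limitations does not mention that control always comes first.

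**The concern.** Randomization protects only what it assigns, and here it assigns the order of MOVE and STAND. It does not assign who is under control conditions or when. The comparison that carries the primary aim therefore has no randomized protection, and the comparison that does have it, MOVE versus STAND, is not a stated aim.

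There is a plausible way for glucose to shift between the baseline week and the later periods whatever the intervention does. At baseline the participants meet the delivered lunches, the fasting window on each side of lunch and the wearable devices for the first time. By the intervention periods these are familiar. Adaptation to any of them would be read as change due to standing or moving.

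What is at stake is the kind of evidence the trial reports. A significant primary result could be presented as a randomized causal effect although the design cannot tell it from a shift after the first week. A shift in the other direction could hide a real benefit.

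**Working it through.** **1. Timeline.** One baseline week, two intervention weeks, at least one washout week and two intervention weeks give 1 + 2 + 1 + 2 = 6 weeks. This reproduces the plan's figure: "The WorkWell Study is a pilot 6-week randomized crossover design with 2 balanced arms". The only control measurement is the first week, and nothing is scheduled in washout.

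**2. Expected values.** Let p0, p1 and p2 be the effects of being at baseline, period 1 and period 2. Let M and S be the intervention effects relative to control, and a and b the sequence means.

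| Sequence | Baseline | Period 1 | Period 2 |
|---|---|---|---|
| MOVE-STAND | a + p0 | a + p1 + M | a + p2 + S |
| STAND-MOVE | b + p0 | b + p1 + S | b + p2 + M |

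Averaging over the two sequences:

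- MOVE − control = M + (p1 + p2)/2 − p0
- STAND − control = S + (p1 + p2)/2 − p0
- MOVE − STAND = M − S

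The occasion effects cancel only in the last line.

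**3. Estimability.** With a free effect for each of the three occasions, the fixed-effects design matrix has 6 columns (intercept, sequence, MOVE, STAND, period 1, period 2) and rank 5. MOVE − control and STAND − control are not estimable; MOVE − STAND is. This follows from the design and needs no assumption about the data.

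**4. The planned period factor.** The article does not say which period level the baseline takes. If it is aligned with period 1, the term p2 − p1 is estimated and removed, and the bias in both control contrasts is p1 − p0. If period is left out, the bias is (p1 + p2)/2 − p0. If time were fitted as a straight line, it is (p1 + p2)/2 − p0 − 1.5(p2 − p1).

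| Shift (p0, p1, p2) | Period 1/2 | No period term | Straight line in time | MOVE − STAND |
|---|---|---|---|---|
| Step (0, 1, 1) | 1.0 | 1.0 | 1.0 | 0 |
| Linear (0, 1, 2) | 1.0 | 1.5 | 0 | 0 |
| Fading (0, 1, 0.5) | 1.0 | 0.75 | 1.5 | 0 |

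Under the planned coding, a one-unit shift from baseline to period 1 adds exactly one unit to both primary contrasts. A later shift between periods 1 and 2 is absorbed.

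**5. Hypothetical illustration of size.** Inputs from Sample Size Calculation are 12 evaluable participants (15 × 0.80 = 12), α = .05 and a planned difference of 15%. The stated 1% SD cannot be the working value: with 15% it would need only 2 or 3 participants. That is a separate matter. I therefore assume the SD of within-person differences at which 12 participants give 80% power in a two-sided paired t-test. The required standardized difference is 0.889, so SD = 15/0.889 = 16.9%. With no true effect and drift d, the noncentrality is d√12/16.9 on 11 degrees of freedom, and the rejection probability is:

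| Drift d | SD 12% | SD 16.9% | SD 25% |
|---|---|---|---|
| 0 | 5% | 5% | 5% |
| 3% | 12% | 8.7% | 7% |
| 5% | 26% | 15.5% | 10% |
| 10% | 75% | 46.5% | 24% |

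The same calculation covers the opposite direction. If the true effect is 15% and a 5% drift opposes it, the net difference is 15 − 5 = 10%. At SD 16.9% the power is then 46.5% instead of 80%.

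**The case against.** The Methods are open about the design: they name a baseline control, say that the intervention sequence is randomized, and place randomization after baseline. The baseline week also has to come first, because each person's hourly goal is the baseline average plus 6 minutes. Meals are repeated across all three periods and the baseline devices are worn again, so differences in conditions are limited. The study is a pilot. All of this stands, and a baseline-first design is legitimate. But standardizing the conditions does not remove habituation to them. Nor does openness in the Methods correct a causal claim in the Discussion.

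Several stronger readings are tempting, and the article does not support them.

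- **That the article expressly credits randomization for the control contrast.** The phrase in the Discussion names no contrast. The fault is that it is not limited to MOVE versus STAND, while the causal claim beside it concerns interrupting sitting, which is the contrast with control.
- **That washout weeks are said to secure nonspuriousness.** They are listed under statistical association, and the article does not say that data are collected in them. Washout can support own-control comparisons by limiting carryover, so Table 1 does not contradict the claim.
- **That any time trend biases the result.** The period term handles a shift between periods 1 and 2, and a strictly linear trend could be removed if modelled as such. The plan does not do so, and one control occasion could not test linearity.
- **Regression to the mean.** Eligibility does not select on glucose.
- **Season.** Rolling recruitment means that participants need not share one seasonal shift.

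Listing MOVE versus STAND as a contrast may be left to an analysis plan that is not shown. The wording of the claim is in the article itself.

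**Conclusion.** The point holds. STAND versus baseline and MOVE versus baseline are nonrandomized before-after contrasts, and the planned model cannot separate the intervention effect from a shift between the baseline week and the intervention periods. Randomization protects MOVE versus STAND only. The Discussion claims more than that, and the limitations do not disclose the fixed order.

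Non-estimability with free occasion effects follows from the design alone. The one-for-one bias under the planned model also assumes that baseline is aligned with period 1. The percentages are hypothetical: the article gives no drift, the 16.9% SD is back-calculated, and a paired t-test stands in for the mixed model. They show how a modest shift would matter at this sample size, not that one is present.

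A reader might go further and conclude that the primary result will be a time effect or that the trial is uninformative. The article does not support that. It supports limiting what the primary result may be called.

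**What to change.** - State in the abstract, aims and discussion that intervention versus baseline is a nonrandomized before-after contrast.
- In Comparison to Prior Work, limit the randomized-assignment claim to MOVE versus STAND and qualify the causal wording to match.
- Note there that no control measurements are scheduled in washout, so washout only limits carryover.
- Add the fixed control-first order to Strengths and Limitations, with habituation to devices, lunches and fasting rules as an example of what it leaves open.
- Report MOVE versus STAND on iAUC, with its confidence interval from the same model, as the only randomized comparison, beside the primary contrasts.
- Word the primary conclusion as change from baseline.

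The cost is some rewording, one more contrast and a less favourable claim. Nothing operational changes. The Results section reports enrollment completed in March 2023, so a redesign with a randomized control period is not realistic, and this fix does not need one.
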